#### Recruitment

All patients admitted to the two rehabilitation wards during the trial period will be screened for inclusion by a senior neurological physiotherapist. Eligible patients will be given information about the project and if they are interested, a research assistant (physiotherapist) will be contacted to provide further information. Written consent will be obtained before participation in the project. Demographic and background information will be collected. Ethical approval for this study has been received from the Human Research Ethics Committee (Tasmania) Network (approval number H0013769).

#### Study design

All participants will undergo two measurement sessions by a physiotherapist blinded to group allocation: one on entry into the study (pre-test) and one after the 8-week period (post-test) or prior to discharge if discharged before 8 weeks. All pre-test measures will be completed prior to randomization.

#### Randomization

Allocation into intervention or control group will be performed by using a computer-generated random number schedule with variable block sizes 2–6. Generation of the randomization sequence will be generated by a researcher not involved in recruitment or assessment. Group allocation will be concealed by using consecutively numbered opaque sealed envelopes, opened in the presence of the participant after completion of assessment.

### Intervention and usual care

Participants in both groups will be assessed by a physiotherapist who will deliver individualised targeted therapy to meet their specific needs.

#### Usual care

In addition to receiving individualised therapy, the usual care group will have a therapist prescribe a series of repetitive exercises (e.g., practice of arm activities, standing up or stepping) in a group setting with physiotherapists or physiotherapy assistants. Usual care varies between the two wards used in this trial. Specific information about usual care for each ward and the delivery plan is provided in Appendix 1.

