## Methods/Design

A single-blind randomized controlled trial will be conducted on two rehabilitation wards of a secondary referral hospital. Participants will be randomly assigned into the JRS WAVE intervention that will last for the duration of the stay on the ward, with a minimum dose of 8 days and maximum of 40 or usual care. All participants will provide written informed consent, and ethical clearance has been received.

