#### Intervention group

JRS WAVE technology use will replace group exercise prescribed in the usual care group or allied health assistant sessions which are usual care on ward two. Participants randomly assigned to the intervention group of this trial will receive individualised prescription of appropriate technology-based exercises to enhance physical activity and mobility. In addition to receiving individualised targeted therapy, each participant will be asked to use the intervention technologies for up to 1 hour each day. As such, both groups will be matched for time in rehabilitation to determine the impact of the technology-based intervention compared with group exercise.

Therapy staff will teach participants to use the equipment and develop individualised exercise programs to enable participants to use the equipment safely. To minimise the risk of contamination, use of the technologies will be done out of sight of control group participants where possible.

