## Appendix

**Table 1 Tab1:** FIND Study Therapy Delivery Plan

	Control	Intervention
Ward One easily fatigued client	Daily individual therapy Functional based	Daily individual therapy Alternating daily functional based therapy and Jintronix
Ward One standard client	AM Group Therapy	AM Jintronix
	PM Individual as required	PM Individual as required
Ward Two easily fatigued client	AM short AHA session	1 short AHA session
	PM short AHA session	1 short Jintronix
	Weekly PT review	Weekly PT review
Ward Two standard client	Daily AHA session	Daily Jintronix + gait/stairs/bed TF
	1-2x / week PT session	1-2x / week PT session
Ward Two client with higher tolerance	Daily AHA session	Daily Jintronix + gait/stairs/bed TF
	4 days / week seated ex group	4 days / week seated ex group
	1-2x / week PT session	1-2x / week PT session
Ward Two client with high tolerance	Daily AHA session	Daily Jintronix + gait/stairs/bed TF
	4 days / wk functional ex group	4 days / wk functional ex group
	1-2x / week PT session	1-2x / week PT session

PT Physiotherapy, AHA Allied Health Assistant, TF transfers

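### Usual care differs by ward, but the stated analysis has no ward term and the described allocation names no ward stratum; the likely cost is precision, not bias

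*Protocol article*

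**What the plan says.** The trial is "conducted on two rehabilitation wards of a secondary referral hospital" (Protocol article, Methods/Design). Under Usual care it states that "Usual care varies between the two wards used in this trial" and points to the appendix for the details.

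The Intervention group section shows that the contrast under test is ward-specific (the ward meant at the end of this quote is the second one): "JRS WAVE technology use will replace group exercise prescribed in the usual care group or allied health assistant sessions which are usual care on ward". Table 1 in the Appendix bears this out for a standard client:

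- Ward One control: "AM Group Therapy", with individual therapy in the afternoon as required. The intervention arm has the technology in the morning instead.
- Ward Two control: a daily allied health assistant session and physiotherapy once or twice a week. The intervention arm has "Daily Jintronix + gait/stairs/bed TF" with the same physiotherapy.

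The Randomization section describes a "computer-generated random number schedule with variable block sizes 2–6" and says "Group allocation will be concealed by using consecutively numbered opaque sealed envelopes". It names no stratification factor and no separate series for each ward.

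The Data analysis section plans t tests or Mann–Whitney U tests, and a repeated measures analysis of variance over time and between the two groups, at the 0.05 level. Ward is not mentioned there.

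**The concern.** Ward is recorded, has two levels, and by the article's own account is linked to the type and frequency of therapy. It is therefore a plausible predictor of activity level, which the Discussion calls the primary outcome of efficacy. It may also be linked to case mix.

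Blocking on a schedule that runs across both wards balances the arm totals. It does not balance the arms within a ward. If one arm happens to hold more participants from one ward, an analysis without ward leaves part of the ward difference in the group estimate. Even when the split is even, variation between wards stays in the residual and widens the confidence interval. A trial of this size has little precision to spare.

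The comparator differs by ward, so the effect of the technology may differ too. A single pooled estimate would not show this.

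**Working it through.** **Inputs from the article (Sample size and justification; Data analysis).** Functional reach SD 7.4 cm; target difference 3.7 cm, so 3.7/7.4 = 0.5 SD; alpha 0.05 (taken as two-sided); power 80%; 63 evaluable and 74 recruited.

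**Assumed, because the article does not give them.** Ward shares, and the between-ward outcome difference g in SD units (0.25 to 1.0).

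**1. The article's own figure.** n per arm = 2(1.96 + 0.84)²/0.5² ≈ 62.8, so 63 per arm and 126 in total. The stated 63 is reproduced per arm but not as a total. With 63 in total (31.5 per arm), power is about 51%. For dropout, 63/0.85 = 74.1, which agrees with 74. The per-arm or total question is a separate matter; 51% is used below only as the starting point.

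**2. Chance imbalance without a ward stratum.** Take 37 per arm and 37 per ward. The number of Ward One participants in one arm is hypergeometric (74, 37, 37). With k of them in that arm, the ward shares differ by |2k − 37|/37. The possible values are 1/37, 3/37, 5/37 and so on, that is 2.7, 8.1, 13.5, 18.9, 24.3 points.

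- P(10 points or more) = P(|2k − 37| ≥ 5) = 0.353
- P(20 points or more) = P(|2k − 37| ≥ 9) = 0.062

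A simulation with permuted blocks of 2, 4 or 6 on one schedule, ward membership left random, and ward shares of 50% to 80% gave:

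| | One schedule | Stratified by ward |
|---|---|---|
| Mean imbalance | 0 | not reported |
| SD of imbalance | 9.5–11.6 points | about 2 points |
| 95th percentile | 19–22 points | 3–4 points |
| Above 10 points | 31–42% | about 0 |
| Above 20 points | 4–8% | about 0 |

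**3. Shift in the estimate, given an imbalance.** Shift = imbalance × g × 7.4 cm, for an endpoint that carries the full ward difference.

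- 10 points: 0.19 cm (g = 0.25), 0.37 cm (g = 0.5), 0.74 cm (g = 1.0).
- 20 points: 0.37, 0.74 and 1.48 cm.

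For scale, the standard error of the group difference is √(4/63) = 0.25 SD at 63 participants, or about 1.9 cm.

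**4. Type I error.** With 74 simulated participants and the unadjusted t test, it was 0.051 (g = 0.5) and 0.050 (g = 1.0) on one schedule. With stratified allocation and still no adjustment, it was 0.048 and 0.028. Stratifying without a ward term therefore makes the test conservative when the wards differ a lot.

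**5. Precision.** With equal wards, total variance = within-ward variance × (1 + g²/4). Power is at 63 in total.

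| g | Ward's share of total variance | 7.4 cm is the total SD: power with a ward term (51% without) | 7.4 cm is the within-ward SD: power without a ward term (51% with) |
|---|---|---|---|
| 0.25 | 1.5% | 52% | 50% |
| 0.5 | 5.9% | 53% | 49% |
| 0.8 | 13.8% | 57% | 45% |
| 1.0 | 20.0% | 60% | 43% |

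**The case against.** **Silence is not a statement.** The article does not say that randomisation is unstratified or that there is one list. A fuller protocol could stratify, and covariates are often left to the analysis plan. This stands as a caution: the article supports only that no ward stratum is described. It carries less weight for the analysis, because the article does name the tests and the model's factors, and ward is not among them.

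**There is no bias.** A reader might infer that ignoring ward biases the trial or produces false positives. The calculations do not support this. The expected imbalance is zero, and the standard error of the unadjusted test already allows for chance imbalance. Any shift depends on the allocation that happens to occur, and can go either way.

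**The size rests on assumptions.** This stands. The article gives no ward sizes or ward differences. The centimetre and power figures use functional reach, whereas the primary efficacy outcome is activity, for which no SD or target is given. A typical imbalance of about 12 points with g = 0.5 shifts the estimate by 0.06 SD, roughly a quarter of a standard error. The larger shifts need a large ward gap together with an uncommon imbalance. For outcomes measured before and after treatment, analysing change removes stable ward differences in level, so less remains to be gained. Activity has no stated baseline, so that relief does not apply to it.

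**Ward is not the only driver of therapy.** Table 1 also varies therapy by fatigue or tolerance within each ward. This is true, but it does not make ward uninformative.

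**Changing the envelopes mid-trial has a price.** Recruitment is under way, participants cannot be blinded, and therapy staff teach the use of the equipment. Lists kept per ward with blocks as small as 2 make the next allocation easier to guess. This stands, and it is why restratification is only optional here.

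**Conclusion.** The point holds as one about efficiency and reporting. The article documents that the comparator differs by ward, and neither the allocation nor the analysis it describes makes use of ward.

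The consequence is lost precision and exposure to chance imbalance: 10 points or more in about 35% of allocations with equal wards, and 31–42% above 10 points in the simulation across ward shares of 50–80%. The power at stake is about 1 to 9 percentage points for assumed ward differences of 0.25 to 1.0 SD, if 7.4 cm is the total SD and the endpoint carries the full ward difference. If the wards differ little, the gain is close to nothing.

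The documents do not support a claim of systematic bias, of inflated type I error, or of an allocation known to be unstratified. A ward term is still worth having, because it uses data already held and costs almost nothing.

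**What to change.** 1. **Analysis.** Include ward as a covariate in every between-group comparison, activity included. One form is a linear model with group, ward and, where it was measured, the baseline value. This also covers participants already enrolled, and no change in sample size is needed for it.
2. **Reporting.** Show the group effect separately for each ward, descriptively, because the comparator differs. Adjustment does not reveal a difference in effect between wards, and the trial is too small to test one reliably.
3. **Clarification.** State in one line whether allocation was stratified by ward. If it was, the ward term is needed all the more, since stratifying without adjusting gave a conservative test at g = 1.0.
4. **Optional.** If allocation is not stratified, keep a separate numbered envelope series per ward for the remaining participants. The drawback is predictability, so blocks of 2 should be avoided.

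Items 1 to 3 cost one model term, one descriptive table and one sentence. Item 4 costs a second envelope series and a documented change to the allocation procedure during recruitment.

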#### Intervention group

JRS WAVE technology use will replace group exercise prescribed in the usual care group or allied health assistant sessions which are usual care on ward two. Participants randomly assigned to the intervention group of this trial will receive individualised prescription of appropriate technology-based exercises to enhance physical activity and mobility. In addition to receiving individualised targeted therapy, each participant will be asked to use the intervention technologies for up to 1 hour each day. As such, both groups will be matched for time in rehabilitation to determine the impact of the technology-based intervention compared with group exercise.

Therapy staff will teach participants to use the equipment and develop individualised exercise programs to enable participants to use the equipment safely. To minimise the risk of contamination, use of the technologies will be done out of sight of control group participants where possible.

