## Discussion

The proposed project will discuss the feasibility and efficacy of the JRS WAVE. Uptake from screening to recruitment, adherence to the intervention and rates of dropout will be discussed. Feedback from clinicians in terms of system utility will be explored. Feedback from clients on the perceived benefits of this type of rehabilitation and enjoyment and ease of use of the games will also be discussed. Changes in pain and fatigue within each session and between the intervention and control groups will be analysed. Differences in activity levels during the two different interventions (JRS WAVE versus group exercise) will be investigated. Between-group differences for outcome measures of upper-limb function as well as balance and mobility will be investigated.

The primary outcome of efficacy consists of the differences in activity levels from using video technology in rehabilitation compared with usual rehabilitation. It will also provide data for new controller- and device-free motion capture software on measures of upper-limb function, balance and mobility. Much of the published research reviewing the effectiveness of interactive technology games with commercial devices has not used motion capture software in a controller-free situation. For example, the wii™ system for balance requires standing on a platform and the upper-limb tasks require the client to hold (or have strapped to their hand if they do not have grasp capacity) a device that the sensor recognises [6].

This software has been iteratively designed with feedback from the clinicians to form a system that meets the needs of stroke clients in the acute hospital setting as they begin their rehabilitation pathway. This system is vastly configurable, giving the clinicians the ability to tailor the program and modify it in an ongoing way to meet the needs of the clients. The different levels of disability of the clients enrolled will provide challenges when determining between-group differences.

Strengths of this study include that it collects feasibility data from both clients and clinicians. It is a well-powered study with an active control group to allow comparisons across a range of functional measures. Also, both groups are matched for time in rehabilitation (rather than the intervention as additional therapy) and this will allow direct comparison of the groups.

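### The contrast stated as technology versus group exercise with time-matched arms is not the one Table 1 sets up: one row of six makes that swap, one row fits no stated replacement, and time matching is asserted but not shown

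*Protocol article*

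**What the plan says.** The Usual care section describes the control exercises as given "in a group setting with physiotherapists or physiotherapy assistants". It adds that usual care differs between the two wards and refers to the Appendix for the delivery plan.

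The Intervention group section makes three statements:

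- A replacement rule: "JRS WAVE technology use will replace group exercise prescribed in the usual care group or allied health assistant sessions which are usual care on ward" (the sentence ends by naming the second ward).
- A dose: "each participant will be asked to use the intervention technologies for up to 1 hour each day".
- A conclusion drawn from these: "both groups will be matched for time in rehabilitation to determine the impact of the technology-based intervention compared with group exercise".

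The Discussion again labels the activity comparison as the technology versus group exercise. It lists as a strength that "both groups are matched for time in rehabilitation (rather than the intervention as additional therapy", and says that this permits a direct comparison of the groups. It also names the difference in activity levels as the primary efficacy outcome.

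Table 1 in the Appendix sets out the control and intervention packages for six kinds of client, two on Ward One and four on Ward Two.

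**The concern.** The text gives a single comparator, group exercise, and an equal amount of therapy in each arm. If the delivery plan provides something else, a difference in activity cannot be reported as the effect of the technology compared with group exercise. It would be the effect of substituting the technology into whatever each ward and type of client normally receives.

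Time matching matters for the same reason. The primary efficacy outcome is physical activity measured by accelerometer, and energy expenditure during rehabilitation is also to be compared. Both depend directly on how long a participant is in therapy. If the minutes differ between arms, the outcome can move without any effect specific to the technology. Matching is also what the Discussion relies on to call the comparison direct.

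**Working it through.** There is no formula to reproduce. The check sets the six rows of Table 1 against the statements in the Intervention group section.

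| Table 1 row | What the technology displaces | Allowed by the replacement rule? | Group exercise in both arms? | Component listed in the intervention arm only? |
|---|---|---|---|---|
| Ward One, easily fatigued | Functional therapy, on alternate days | No | None in either arm | No |
| Ward One, standard | Morning group therapy | Yes | No | No |
| Ward Two, easily fatigued | One of two short assistant sessions | Yes | None in either arm | No |
| Ward Two, standard | Daily assistant session | Yes | None in either arm | Yes |
| Ward Two, higher tolerance | Daily assistant session | Yes | Yes | Yes |
| Ward Two, high tolerance | Daily assistant session | Yes | Yes | Yes |

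**The contrast.** Technology takes the place of group exercise in 1 of 6 rows, of assistant sessions in 4 of 6, and of neither in 1 of 6 (1 + 4 + 1 = 6). In 2 of the 4 Ward Two rows the exercise group runs in both arms; one of them shows "4 days / week seated ex group" for control and intervention alike. In those two rows group exercise is common to the arms, so it cannot be the contrast.

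**The row outside the rule.** For the Ward One easily fatigued client, control is daily individual functional therapy and intervention is "Daily individual therapy Alternating daily functional based therapy and Jintronix". The rule names two things that the technology replaces, group exercise and Ward Two assistant sessions, and this row contains neither. The table above reads the alternation as taking place within the daily individual session. If it is instead an added session, the intervention arm has more therapy than control, and the matching claim fails for that row. Neither reading agrees with the text.

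**Time matching.** Let c be the minutes of the control session, t the minutes of technology and g the minutes of any listed component beside it. The arms match in that slot only if t + g = c.

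- t is bounded above by 1 hour and is not fixed, so a match does not follow from the dose sentence.
- c and g are not given: Table 1 states minutes in 0 of 6 rows.
- In 3 of 6 rows the intervention cell reads "Daily Jintronix + gait/stairs/bed TF" against a daily assistant session in control. If the added work lies outside the slot and t = c, the intervention arm exceeds control by g. If it lies inside the slot, t = c − g: the arms match, but the technology fills only part of the session.

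The table therefore neither confirms nor refutes equal time.

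**The case against.** The strongest defence is that the text does not promise a pure swap with group exercise. The replacement rule names Ward Two assistant sessions, and the Usual care section says that care differs by ward. That stands: all four Ward Two rows obey the rule, and the direct conflict with it is confined to the Ward One easily fatigued row. It does not rescue the summary label, which drops the assistant sessions and speaks only of group exercise.

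A second defence is that session lengths may be in a full protocol that is not shown. Their absence from the article is therefore no fault in itself. What can be faulted is that the article derives matching from a ceiling and then counts it as a strength.

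Several stronger readings are tempting but not supported:

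- **That Table 1 contradicts time matching.** It gives no minutes and cannot do so.
- **That the intervention arm receives extra gait practice.** The content of the control assistant session is not itemised and may already include gait, stairs and transfers.
- **That Ward One easily fatigued clients lose individual therapy.** Both cells open with daily individual therapy, and the sessions may remain with changed content.
- **That most participants do not receive the stated contrast.** Rows are not participants, and no frequencies by row are given.
- **That the fatigue or tolerance category could be chosen after allocation.** The article does not say when it is set. Silence on such a detail in a condensed article is not evidence.
- **That the shared exercise group biases the comparison.** It is a co-intervention listed equally in both arms, and it does not by itself expose control participants to the technology.

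**Conclusion.** The point holds as a mismatch between the stated contrast and the delivery plan. Group exercise is swapped for the technology in one row of six and kept in both arms in two. One row conflicts with the replacement rule. Time matching is asserted without support, and the component listed in one arm only in three rows puts it in doubt without disproving it.

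These counts take Table 1 as the plan to be delivered, as the Usual care section presents it. They describe client types, so the share of the sample affected is unknown. The randomised comparison of the two packages as delivered is not called into question. What changes is the conclusion that can be drawn from it: neither technology versus group exercise nor a direct, time-matched comparison is supported as the text stands.

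**What to change.** 1. Reconcile the Intervention group section and the Discussion with Table 1, including the Ward One easily fatigued row and the meaning of the added gait, stairs and transfer work. Which schedule is right is for the investigators to settle; this review takes no position.
2. State the contrast and the conclusion as technology substituted within ward-specific usual care.
3. Add delivered minutes by therapy type (technology, group, assistant, individual) to the existing session record, for every participant in both arms. The protocol already records sessions undertaken and reasons for missed sessions, and collects ratings after each session in both groups, so this adds fields to an existing process.
4. Report total minutes by arm, and claim time matching only if the totals agree. Otherwise give the difference alongside the activity result.

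The cost is slightly more data recording and a narrower conclusion. The Trial status section says that recruitment is still under way, so recording can begin for the remaining participants. Minutes may not be recoverable for those who have already finished, and the report should say so.
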